## Abstract

**Introduction:**

Treatment expectations are a key mechanism of placebo effects in clinical trials. In a previous study (PSY-HEART-I), preoperative expectation optimisation improved quality of life 6 months postcardiac surgery. However, barriers such as travel distance, staffing shortages and COVID-19 limited participation. This study evaluates the feasibility and acceptability of iEXPECT, a brief internet-based intervention designed to optimise expectations before heart surgery.

**Methods and analysis:**

In this three-arm, multicentre randomised controlled trial, 160 patients undergoing elective coronary artery bypass graft surgery are randomised to: (a) standard of care (SOC); (b) SOC plus iEXPECT with phone-based guidance (iEXPECT enhanced) or (c) SOC plus iEXPECT with email-based guidance (iEXPECT limited). The intervention includes four 20 min online modules addressing surgical benefits, side effects and coping strategies. Modules are accompanied by personalised guidance provided through feedback on each module via email or telephone (three before surgery, three booster sessions at 6, 12 and 18 weeks postsurgery). Assessments occur at baseline (5–21 days before surgery), preoperatively (day before surgery), 7 days postsurgery and 6 months later. Primary feasibility outcomes include recruitment (≥1 participant/week/centre), retention (≥49% completing 6-month follow-up including biomarkers) and engagement (≥75% completing ≥1 presurgery module). Acceptability is measured by self-reported enjoyment, usefulness and impact, with acceptance defined as mean scores >3.4 (5-point Likert scale) and CSQ-I ratings. Secondary outcomes include psychological measures, inflammatory markers and heart rate variability.

**Ethics and dissemination:**

Ethical approval was granted by the Ethics Committees of Philipps University Marburg (AZ 229/23 BO) and the University of Giessen (AZ 186/23). All participants provide written informed consent. Results will be shared via publications, conferences and public outreach with relevant consumer advocacy groups.

**Trial registration number:**

DRKS00033284.

Strengths and limitations of this studyInvolving three diverse clinical centres enhances generalisability and feasibility assessment across different hospital settings.Use of stratified, permuted block randomisation via REDCap, a secure platform for managing online databases and surveys, ensures allocation concealment and minimises selection bias.Medical staff (caregiver, treating physician) remain blinded to group assignment, reducing the risk of biased treatment effects.Although previous patient feedback informed intervention development, there was no structured patient involvement in designing the current trial.Digital intervention format excludes patients without internet access or sufficient digital literacy, potentially limiting inclusivity.

## Introduction

 One of the treatment options for patients with coronary heart disease (CHD) is coronary artery bypass grafting (CABG), where a surgically created blood vessel bridge aims to restore blood flow.^1^ While many individuals typically experience improvements in their overall health after heart surgery, not everyone has a smooth recovery. Some patients encounter challenges, such as diminished vitality, limited physical functioning, mediocre general health and bodily pain.^2^ For a substantial number of individuals, their health and quality of life may not show the expected improvement and may possibly deteriorate even further, despite the surgery being successful from a medical perspective.^3 4^ Preoperative expectations and illness beliefs play a crucial role in postoperative recovery and predict outcomes following heart surgery.^5^ These expectations, as one crucial mechanism of the placebo effect in clinical studies, are integral to medical procedures and contribute significantly to their success.^6 7^ This phenomenon extends beyond medication to surgeries and other medical procedures, underlining the pervasive influence of patient expectations.^8^,^10^

Enhancing patients’ expectations before surgery may help optimise postoperative outcomes. For this reason, the expectation-optimising intervention ‘EXPECT’ was developed as a preoperative psychological intervention to enhance patients’ benefit expectations, side-effect expectations and personal control/coping expectations (for a detailed intervention manual see^11 12^). The ‘EXPECT’ intervention comprised two face-to-face sessions and two telephone calls before the operation, complemented by a postoperative follow-up phone call.^12^ The pilot study (PSY-HEART-I trial) demonstrated that optimising preoperative expectations through the ‘EXPECT’ intervention had lasting positive effects on health outcomes, including reduced disease-related disability, improved quality of life, increased physical activity and shorter hospitalisation duration following bypass surgery.^13 14^ In the ongoing multicentric follow-up project (PSY-HEART-II trial), the effectiveness of the ‘EXPECT’ intervention is being explored on a broader scale at ten different study centres.^15^ Despite substantial demand, many patients faced barriers preventing their participation, such as long travel distances, scheduling issues and time constraints. The COVID-19 pandemic further complicated these efforts at surgical sites, underscoring the need for new strategies to improve preoperative preparation and ensure broader access to the intervention that can optimise treatment outcomes.

An internet-based adaptation of the ‘EXPECT’ intervention could offer significant benefits due to its scalability. By requiring fewer in-hospital resources and allowing patients to prepare from home, it can overcome geographical and time-related barriers, making optimal preoperative care accessible to a wider patient population.^16^ For a range of different mental disorders, therapist-guided internet-based cognitive-behavioural therapy has proven more effective than waitlist control conditions and has shown similar effectiveness to face-to-face interventions.^17^ Despite this success, no studies have examined the effects of an internet-based preoperative psychological intervention before heart surgery.

In a previous step, the traditional face-to-face ‘EXPECT’ intervention for expectation optimisation was adapted into an online format (iEXPECT). The present study—the iHEART trial—aims to test the feasibility of the study design and the acceptability of the online, preoperative, guided psychological iEXPECT intervention. Specifically, the primary objectives are to evaluate (1) the feasibility of implementing the study design across multiple sites, similar to the PSY-HEART-II trial, (2) whether patients are able and willing to engage with the intervention as intended and (3) the acceptability of the iEXPECT intervention from the patients’ perspective. Given the uncertainty around the optimal level of guidance for online interventions,^18 19^ this study will also explore two variations of the online intervention, each offering different levels of therapist support (enhanced vs limited interaction). Secondary outcomes include psychological and physiological measures that will be analysed descriptively per group. Biomarkers will be collected to assess the feasibility of obtaining inflammatory markers and heart rate variability (HRV).

This feasibility trial also serves as a precursor to a larger future study (Phase III trial) aimed at evaluating the efficacy of the iEXPECT intervention. If successful, the iHEART trial could counteract the previous barriers and could thus improve access to better healthcare for patients undergoing heart surgeries.

## Materials and analysis

### Registration and funding

The trial has been preregistered at the German Clinical Trials Register (https://www.drks.de/DRKS00033284). It is funded by the German Research Foundation (DFG) (SA 4505/3–1 PI [name]). For detailed information, see the online supplemental table S1, which contains all items of the WHO Trial Registration Data Set.

### Study design

The iHEART trial is a three-arm, multicentre, randomised controlled trial that examines the feasibility and acceptance of a guided preoperative internet-based intervention aiming to optimise treatment outcome expectations (iEXPECT) in addition to standard of care (SOC). The content, derived from the face-to-face ‘EXPECT’ intervention,^11 15 20^ aims to improve individual expectations, enhancing recovery for cardiac surgery patients through placebo effects.^12 14 20^ Adapted to an online format, the intervention covers three main components to promote personalised, positive, realistic expectations and correct dysfunctional beliefs: (1) benefit expectations of surgery, (2) personal control strategies (eg, health behaviour, lifestyle) and (3) coping with negative postoperative effects (see table 1). These aspects of the intervention are expected to influence psychological factors and yield improvements such as reducing anxiety levels or depressive symptoms. As part of the intervention, guidance is provided through personalised feedback via phone calls (iEXPECT enhanced) or via email (iEXPECT limited). Participants will be recruited and data collected at the three participating centres: the university hospital of Marburg, the university hospital of Gießen and the medical centre Kerckhoff-clinic, Bad Nauheim. Figure 1 shows the study flow chart.

**Figure 1 F1:**
[figure not shown]
Study flow chart of the iHEART Study. Expectation manipulation online intervention (iEXPECT), standard of care (SOC), coronary artery bypass graft surgery (CABG), days (**d**). Assessments take place 5–21 days before the surgery (baseline, (**T0**), preoperatively on the day of hospital admission after the psychological intervention (**T1**), 7 days after surgery (**T2**) and follow-up, 6 months after surgery (**T3**). The iEXPECT interventions include four modules (20 min), of which the first three are guided, before the surgery, and three guided booster sessions 6, 12 and 18 weeks after the surgery.

**Table 1 T1:** Module overview of the preoperative psychological iEXPECT online intervention

Module names	Content
Benefits of the CABG surgery	Welcome and introduction to the study platform (minddistrict.com). Psychoeducation on CHD and disease model. Benefits of the CABG surgery. Developing a personalised step-by-step recovery action plan (eg, go for a walk: in the first 6 weeks after surgery, lawnmowing: 6 weeks after surgery, heavy gardening: 3 months after surgery). Imagination exercise ‘6 months after a successful surgery—the best possible self’.
Personal control strategies (eg, health behaviour, lifestyle choices)	Information on risk factors and health behaviours. Individualised health behaviour plan. Emphasises personalised outcome expectations and self-efficacy. Imagination exercise ‘6 months after a successful surgery—the best possible self’.
Negative postoperative side effects and coping strategies	Temporary side effects like incision pain and waking in the ICU are discussed to reassure patients. Expectations for treatment outcomes and timelines are clearly explained. Developing personalised coping expectations. Imagination exercise ‘6 months after a successful surgery—the best possible self’.
Summary	Summary of the key content from modules 1–3. Imagination exercise ‘6 months after a successful surgery—the best possible self’.
Booster (1–3)	Key topics from the previous modules (eg, health behaviour maintenance, risk factors and personal control strategies). Gather feedback on complications or successful experiences. Imagination exercise ‘6 months after a successful surgery—the best possible self’.

Following modules (1–3) completion, patients receive personalised guidance via telephone call (iEXPECT enhanced) or via email (iEXPECT limited) on the content from the iHEART study team. All modules (at least 1–3) should be completed by no later than 1 day before the heart surgery.

CABG, coronary artery bypass graft; CHD, coronary heart disease; iEXPECT, expectation manipulation online intervention.

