### Secondary outcomes

Secondary outcomes include multimodal assessments (ie, self-ratings, expert ratings, clinical facts, biological measures) that were selected to capture a comprehensive picture of psychological, behavioural and clinical processes that may be affected by the intervention and are relevant for evaluating its broader impact and future Phase III trial feasibility. These include measures of preoperative anxiety and need for information (APAIS, Amsterdam preoperative anxiety and information scale),^28 29^ general anxiety and depression (PHQ9, patient health questionnaire; and GAD-7, generalized anxiety disorder scale),^30 31^ and treatment expectations (TEX-Q, treatment expectation questionnaire; and GEEE, generic rating scale for previous treatment experiences),^32 33^ all of which are known to influence surgical outcomes and psychological readiness. We also included constructs such as attitudes towards internet-based interventions (APOI, attitudes towards psychological online interventions),^34^ subjective illness beliefs (B-IPQ, brief-illness-perception questionnaire),^35^ social support (ESSI-D, enriched social support inventory-deutsch)^36^ and trait optimism (LOT-R, revised life orientation test),^37^ which may moderate treatment engagement and response. Furthermore, indicators of digital health literacy (GR-eHEALS, revised German eHealth literacy scale),^38^ physical activity (IPAQ, international physical activity questionnaire),^39^ perceived stress (PSS, perceived stress scale),^40 41^ illness-related disability caused by the current medical condition (PDI, pain disability index adapted version),^22^ pain (VAS, visual analogue scale, 0–10), quality of life (SF-12, short-form health survey)^42^ and treatment satisfaction (ie, rating of fulfilment/violation of pretreatment expectations at the end of the trial) may provide a multidimensional view of patient functioning across time. To explore potential adverse effects and unmet needs, we assess negative side effects (NEQ, negative effects questionnaire)^43^ and prior pretreatment experiences. The following clinical parameters are also included to explore associations between psychological factors and physical recovery: rehospitalisation; length of stay; length of time at intensive care unit; planned and realised surgery; EURO-Score II, European system for cardiac operative risk evaluation^44^; CSS score, Canadian Cardiovascular Society^45^; blood pressure; LVEF, left ventricular ejection fraction; New York heart association (NYHA) score; complications; inflammatory processes (C reactive protein (CRP), IL-6, Interleukin-6, IL-8, Interleukin-8); HRV, heart-rate-variability (ie, triangular index).

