
### Assessment

Assessments take place 5–21 days before the surgery (baseline, T0), preoperatively on the day of hospital admission after the psychological intervention (T1), 7 days after surgery (T2) and 6 months after surgery (T3) (for an overview, see figure 2). Psychological data will be collected through questionnaires (eg, regarding disease-related impairment, quality of life, depression and anxiety) and takes place online via the secure web-based survey platform UniPark (https://www.unipark.com/). At each assessment point (T0–T3), completion of the psychological questionnaires will require approximately 30 min. Participants are encouraged to complete them online via UniPark, although paper-based versions may be provided by clinical staff in cases of technical difficulties, and retention is supported through personalised email invitations, reminder emails and phone calls. These strategies have been shown to enhance compliance and reduce attrition,^46^ helping to ensure complete data collection across all time points. Patients will be asked to complete the questionnaires and to contact study therapists if they have any questions. For a detailed overview, see the online supplemental table S2, which shows the applied questionnaires, biological parameters and case report forms (CRFs). Furthermore, semistructured interviews with a small subset of CABG patients (up to N=12) will be conducted on a voluntary basis after surgery to retrospectively explore preparation needs and qualitatively assess the intervention. Interviews (30–45 min) will be audio-recorded, transcribed and analysed using qualitative content analysis.^47^ All data will be anonymised.

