#### Collection procedure

Blood samples will be taken outside of fasting periods to examine plasma levels of inflammatory markers (CRP, IL-6) at each assessment point (T0–T3). Patients will be either sitting or lying down to minimise the impact of movement or physical activity on the results. Prior to blood collection, patients will rest for 30 min. Once collected, blood will be placed into polyethylene tubes with EDTA as an anticoagulant (S-Monovette; Sarstedt, Nümbrecht, Germany), then promptly transported on ice to the laboratory. There, samples will be centrifuged at 2000 g for 10 min in a refrigerated centrifuge (4°C). Plasma aliquots will be stored at −80°C until analysis. Blood samples will be obtained by the study team in Marburg and sent to Essen for analysis by [name] and his team at the Institute of Medical Psychology and Behavioral Immunobiology at the University Clinic Essen. Variability coefficients will be calculated for both intra-assay and interassay precision. The procedure will remain consistent across all treatment groups. Once analysis is complete, blood samples will be discarded. Heart rate will be recorded as beat-to-beat intervals using Polar H10 sensors with chest straps and the Elite HRV application on Android phones at 1000 Hz.^54^,^56^ Beat-to-beat intervals will measure the time between successive R-spikes. To analyse HRV indices such as RMSSD (‘Heart Rate Variability’, 1996), we will record at least 5 min of heart rate activity while patients are sitting. Data will be collected and documented through an electronic CRF (eCRF/EDC-System) hosted by KKS Marburg, with secure web-based data entry (HTTPS (TSL/SSL) and supplementary outcome information, including any complications.

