
Baseline characteristics will be presented by group. For categorical variables, the number of patients per category will be reported as well as the category proportion. The number of missing values will also be presented. For continuous variables, mean and SD will be reported. Primary and secondary outcome variables will be analysed in the same way at the predefined timepoints. Secondary outcomes will be analysed descriptively to identify relevant trends, inform intervention refinement and guide power calculations for a future Phase III trial. While the study is not powered to detect efficacy, exploratory correlation and regression analyses may be performed to examine relationships among secondary outcome variables and to generate hypotheses for subsequent confirmatory research.

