## Ethics and dissemination

### Ethics

The research involving human participants underwent review and received approval from the Ethics Committee of the Department of Medicine at Philipps University of Marburg (Approval Number: AZ 229/23 BO; Date: 8 November 2023) and the Ethics Committee of the Department of Medicine at the University of Giessen (Approval Number: AZ 186/23 Date: 5 February 2024) for the study centres in Giessen and Bad Nauheim. All patients will voluntarily provide written informed consent to participate in the study. The protocol conforms to the Declaration of Helsinki, ensuring that patients receive standard medical procedures. Any modifications to the protocol require amendments in consultation with both Ethics Committees and will be communicated to investigators and participants. Detailed written patient information and consent are provided in the online supplemental appendix. Patients can contact the study management at any time during and after the study period. The trial will end once the target sample size is reached.

Patients who decline participation at specific assessment time points will still be contacted at later time points, where appropriate, to explore reasons for withdrawal and gather relevant follow-up information. Patients in the iEXPECT condition may decline individual conversations but will continue participation without any changes. Any deviations from the protocol will be recorded, and adverse events will be documented and reported immediately to the principal investigators. The principal investigators will evaluate these adverse events and provide guidance on how to handle them.

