### Feasibility

We anticipate high feasibility for the study as patients are not required to attend additional appointments at the clinic prior to hospital admission. In the ongoing PSY-HEART-II trial, we recruited approximately 110 patients over 12 months using ten centres. However, recruitment was significantly hindered by two waves of the COVID-19 crisis, which led to the postponement of all elective surgeries. The iHEART trial only necessitates that patients have regular access to a computer with an internet connection and a valid email, thus avoiding additional travel costs and patient journeys. The only extra effort required from patients is the time needed to complete the questionnaires and the intervention. Booster emails (iEXPECT limited) or phone calls (iEXPECT enhanced) are scheduled at 6, 12 and 18 weeks after patients return home. We plan to recruit approximately 160 patients in 12 months (plus a 6-month follow-up) with three participating centres, given that the recruitment process will not be complicated by the COVID-19 crisis.

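### Only the two iEXPECT arms have booster contacts that ask about complications, so by-arm complication and adverse-event proportions may be inflated there unless the source of each event is recorded

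*Protocol article*

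**What the plan says.** - **Booster content.** Table 1 of the protocol article (under Study design) lists, for Boosters 1–3: "Gather feedback on complications or successful experiences".
- **Who has boosters, and when.** The Figure 1 legend makes "three guided booster sessions 6, 12 and 18 weeks after the surgery" part of the iEXPECT interventions. The Discussion (Feasibility) gives the mode by arm: "Booster emails (iEXPECT limited) or phone calls (iEXPECT enhanced) are scheduled at 6, 12 and 18 weeks after patients return home". The two places count the weeks from different starting points, which does not matter for this point.
- **Contacts common to all arms.** Under Assessment, the postoperative assessments are "7 days after surgery (T2) and 6 months after surgery (T3"). No SOC contact is described in between.
- **Outcomes concerned.** Secondary outcomes lists rehospitalisation and also "New York heart association (NYHA) score; complications; inflammatory processes". The Introduction says that secondary outcomes are described per group, and the Data analysis plan says: "Primary and secondary outcome variables will be analysed in the same way at the predefined timepoints".
- **Recording.** Under Ethics, "adverse events will be documented and reported immediately to the principal investigators", with no limit on how the team learned of the event. Under Collection procedure, the electronic case report form takes "supplementary outcome information, including any complications", also without naming a source.

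**The concern.** The chance that a post-discharge event becomes known to the study team can depend on the arm. Scheduled contacts between T2 and T3 number 3 (enhanced), 3 (limited) and 0 (SOC). A live call may also draw out more than an email, so the two iEXPECT arms may differ from each other. If what is learned at a booster is entered in the record that is later summarised by group, more questioning can read as more harm.

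At stake are the by-group descriptions of complications, rehospitalisation and adverse events. The Data analysis plan uses the secondary outcomes to refine the intervention and to plan the Phase III trial. Recruitment, retention, engagement and acceptance are not touched.

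**Working it through.** The plan gives no complication rate and no capture rate, so it has no figure of its own to reproduce. The rates below are assumptions, shown as ranges.

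**Inputs from the article:** boosters at weeks 6, 12 and 18; T2 at week 1; T3 at 6 months (week 26); arm sizes 64, 64 and 32 (Sample size and study power).

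**Assumptions:** the true event rate is the same in all arms. Events are spread evenly over weeks 1 to 26. An event is captured at T3 with probability p, and at each booster held after it with probability q, independently. Booster reports enter the record.

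**Step 1. Share of events by number of boosters still to come**
- Weeks 1–6: 5/25 = 0.20, three boosters
- Weeks 6–12: 6/25 = 0.24, two
- Weeks 12–18: 6/25 = 0.24, one
- Weeks 18–26: 8/25 = 0.32, none

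**Step 2. Capture.** In SOC it is p. In a booster arm it is 1 − (1 − p) × S, where S = 0.20(1 − q)³ + 0.24(1 − q)² + 0.24(1 − q) + 0.32.
- q = 0.25: S = 0.084 + 0.135 + 0.180 + 0.320 = 0.719
- q = 0.5: S = 0.025 + 0.060 + 0.120 + 0.320 = 0.525
- q = 0.8: S = 0.002 + 0.010 + 0.048 + 0.320 = 0.379 (terms rounded)

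**Step 3. Apparent risk ratio (booster arm / SOC)**

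| p | q = 0 | q = 0.25 | q = 0.5 | q = 0.8 |
|---|---|---|---|---|
| 0.49 | 1.00 | 0.633/0.49 = 1.29 | 0.732/0.49 = 1.49 | 0.807/0.49 = 1.65 |
| 0.80 | 1.00 | 0.856/0.80 = 1.07 | 0.895/0.80 = 1.12 | 0.924/0.80 = 1.16 |
| 1.00 | 1.00 | 1.00 | 1.00 | 1.00 |

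The value 0.49 is borrowed from the retention criterion. That criterion concerns complete T3 data including biomarkers, so a patient without a blood sample can still report a complication. The row is a pessimistic bound.

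**Step 4. In patients.** At a true rate of 20%, with p = 0.49 and q = 0.5, the recorded rate is 0.20 × 0.732 = 14.6% in a booster arm and 0.20 × 0.49 = 9.8% in SOC. On 32 SOC patients that gap is 0.048 × 32, about 1.5 patients.

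**Step 5. Cross-check with a simpler model.** Let c be the share captured by routes common to all arms, and b the share of the remainder captured at boosters. The ratio is 1 + b(1 − c)/c. With b from 0.25 to 0.75 it is 1.03–1.08 at c = 0.9, 1.11–1.32 at c = 0.7 and 1.25–1.75 at c = 0.5. It is 1.00 when b = 0 or c = 1.

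**Step 6. Against chance.** With a true rate of 30%, c = 0.7 and b = 0.5, exact binomial calculation gives the pooled iEXPECT arms (128) a higher recorded proportion than SOC (32) in about 70% of trials. With equal ascertainment (b = 0) the figure is about 49%.

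**The case against.** The strongest reply is that the link from booster to record is assumed. Table 1 describes therapeutic content: complications are paired with successful experiences and sit beside an imagination exercise. Nothing says that this feedback reaches the adverse-event form or the complication item. The Data analysis plan ties outcomes to predefined timepoints, and boosters are not among T0–T3, so the complication outcome may already rest on common timepoints. Supplemental table S2 and the case report forms, which are not shown, may settle the matter. All of this stands, and it is why the point is conditional. It does not remove the point: the adverse-event sentence under Ethics is not limited by source, and a therapist told of an event at a booster would ordinarily document it.

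The size is also open to challenge. The model gives SOC no hospital-record route, leaves out complications before T2 (which boosters cannot affect), and treats booster and T3 response as independent. Each of these pushes the ratio up, so the upper end should not be read as an expectation.

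Three stronger readings are tempting, and the article supports none of them:
- That the iEXPECT arms will look worse. The ratio may be 1.00, and even with inflation chance can reverse the order in arms this small.
- That the Independent Data Monitoring Committee will see a distorted by-arm comparison. Its section mentions updates on serious adverse events and no display by arm.
- That the boosters conceal harm. Extra ascertainment raises counts; at most it invites a reader to dismiss a real excess.

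One could also leave the matter to the analysis plan. But an analysis plan can separate sources only if the source was recorded when the event was reported.

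**Conclusion.** The concern holds in conditional form. Opportunity to detect post-discharge events differs by arm (3, 3 and 0 scheduled contacts), and the article does not say whether booster reports feed the by-group record. If they do, recorded proportions in the iEXPECT arms may be inflated with no true difference, possibly more in the telephone arm. The apparent risk ratio runs from 1.00, through about 1.1 with 80% capture at T3, to about 1.65 with 49%; the simpler model reaches 1.75 when common routes capture only half. All of these rest on assumed capture rates. The consequence is confined to descriptive secondary and safety data used for Phase III planning. No test is planned on these outcomes, and the primary criteria are unaffected. It is a cheap improvement, worth making while follow-up is running because the source of an event is hard to reconstruct later.

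**What to change.** - Keep documenting and acting on every event, however it is learned.
- Record the source of each event: booster, spontaneous report, T2/T3 or hospital record.
- State whether booster reports enter the adverse-event and complication record.
- Base between-arm displays of complications, rehospitalisation and adverse events only on sources and timepoints common to all three arms (T2, T3, hospital records), as proportions, since the arms are 64, 64 and 32.
- List booster-only events separately, as information available in the iEXPECT arms only.

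The cost is one field on the adverse-event form and one sentence in the analysis plan, or the sentence alone if the form already holds the source. Patients carry no added burden. The downside is that the comparative tables contain fewer events, with the rest in the separate listing.
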